#### Mental illness-related stigma

Mental illness-related stigma will be measured by the 10-item version of the Internalized Stigma of Mental Illness Scale (ISMI-10) [82], which has been validated in Ethiopia [49, 83].

#### Post-trauma-related cognitions

Trauma-related cognitions will be assessed by the Post-Traumatic Cognitions Inventory [84] which is a 36-item measure assessing negative and inaccurate thoughts that are common in people with PTSD.

#### Self-reported arousal

The Self-Assessment Manikin (SAM) will be used to assess three domains of present-moment affective state: valence (e.g., positive or negative), arousal (e.g., calm or excited), and dominance (e.g., powerful or weak). Each affective domain is rated by participants on a 5-point scale using pictures [85].

#### Psychophysiological arousal

If found to be feasible, acceptable, and accurate following usability testing, physiological arousal will be measured by increases in heart rate variability [86, 87] using the Empatica E4 wristband wearable device [88] and Mindfield ESense Skin Response system [89] during the PhenX Toolkit’s trauma challenge assessment [90] which was adapted from Foa & Rothbaum’s Standardized Trauma Interview [91], in which participants will be asked to think about and recount details of their traumatic experiences. Similar to other trauma assessment questionnaires and interviews, the PhenX Toolkit’s trauma challenge assessment interview asks about a participants’ trauma experiences and assesses symptoms, while also assessing physiological arousal before during and after discussion of the trauma experiences and symptoms [90, 92]. At each assessment time point, data will be collected for a total of 15 min including 5 min during baseline, 5 min during the trauma interview, and 5 min during the trauma imagery.

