**Methods:**

Specifically, this study includes a non-randomized pre-pilot (*n* = 5) and a randomized feasibility trial comparing BREATHE Ethiopia to Treatment as Usual (*n* = 40) to assess trial procedures, acceptability, and feasibility of intervention delivery, and investigate potential effectiveness and implementation. In a process evaluation, we will collect data that will be critical for a future fully randomized controlled trial, including the numbers of participants who are eligible, who consent, who engage in treatment, and who complete the assessments, as well as the feasibility and acceptability of assessments and the intervention. Qualitative data on facilitators and barriers to intervention delivery and quantitative data on provider fidelity to the intervention and participant and provider satisfaction will also be collected. Quantitative assessments at baseline, post-treatment, 1-month follow-up, and 3-month follow-up will assess change in mental health symptoms and functional impairment and hypothesized intervention mechanisms, including knowledge about PTSD, stigma, trauma-related cognitions, and physiological arousal.

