The intervention consists of three main parts spread over five brief treatment sessions: (1) breathing retraining: participants are taught and encouraged to use breathing retraining to reduce current or anticipated physiological arousal that is associated with anxiety. Breathing retraining is taught in the first session and reviewed in all subsequent sessions; (2) normalizing through psychoeducation: the intervention teaches participants and (with participants’ permission) their families about the commonness of trauma, trauma symptoms, and related problems so that they understand that their reactions are normal and experienced by other people too. This information is presented using information handouts, worksheets, and discussion; and (3) positive coping: the intervention provides information about the relationship between PTSD symptoms and related problems and encourages participants to use positive coping strategies to help them feel better and more able to achieve their goals.

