### Quantitative data analyses

With a small sample size, the analyses will be descriptive and exploratory and will primarily be used to inform a future fully powered trial. We will calculate descriptive statistics to assess participation, retention, satisfaction, and fidelity. We will explore the relationship between covariates and baseline outcome scores and retention, satisfaction, and fidelity to identify any characteristics that might be associated with higher or lower implementation success. In addition, we will calculate summary statistics on all treatment mechanisms, mental health outcomes, and covariates of interest. We will investigate how scores on the outcome measures listed above change over time, paying particular attention to change between baseline and post-intervention scores and comparison between the intervention and the TAU groups. We will conduct bivariate analyses to assess the association between covariates and outcomes. Participant and caregiver reports will be analyzed separately. For continuous outcomes, we will use mixed-models with the participant as the random intercept to assess repeated measures change over time. This approach was selected because it models all available data regardless of whether individuals were missed at some time points. If deemed necessary, we will employ variable transformation techniques to improve the normality assumption. The analysis will include all participants who completed the baseline assessment and at least one treatment session, effects of outlier data inclusion in analyses will be assessed, and if necessary missing data will be handled using multiple imputation. Given the aim of the study to assess feasibility and implementation and the low sample size, differences in comorbidities will not be a main focus of analysis. Future larger iterations of the protocol will take these into account.

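### Physiological arousal is defined as a rise in heart rate variability, opposite to the accepted direction, so calming would be read as more arousal on this conditional, exploratory measure

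*Protocol article*

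**What the plan says.** The Psychophysiological arousal section of the protocol article makes the measure conditional: "If found to be feasible, acceptable, and accurate following usability testing", it will be used. It then defines the measure: "physiological arousal will be measured by increases in heart rate variability". Two devices are named for it, a wristband and the "Mindfield ESense Skin Response system". Recording takes place during a trauma challenge in three segments: "5 min during baseline, 5 min during the trauma interview, and 5 min during the trauma imagery".

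Three other places bear on the direction and weight of this measure.

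- The Intervention section says participants are taught "breathing retraining to reduce current or anticipated physiological arousal that is associated with anxiety".
- The Methods part of the Abstract places arousal among the "hypothesized intervention mechanisms, including knowledge about PTSD, stigma, trauma-related cognitions, and physiological arousal".
- Quantitative data analyses says that "the analyses will be descriptive and exploratory and will primarily be used to inform a future fully powered trial". It also plans a comparison of the two arms and of change over time, with most attention to change from baseline to after the intervention.

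Heart rate variability is mentioned only in the Psychophysiological arousal section. No index of variability is named, and skin response is given no direction.

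**The concern.** A mechanism measure is useful only if its direction is right. The treatment theory is that breathing retraining lowers arousal, and the trauma challenge is where that should show. If arousal is equated with a rise in heart rate variability, the physiological pattern expected from a calmer participant is labelled as the pattern of a more aroused one.

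This is a rule the article states, in a direction that conflicts with general physiology. It is therefore different from a scoring detail left to a fuller document. An analysis plan that follows the sentence inherits the error, and one that departs from it contradicts the published protocol.

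At stake is how the between-arm comparison on this one mechanism is read when the results are used to plan a later, fully powered trial.

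**Working it through.** The protocol gives no figure to reproduce, and no power, alpha or effect size enters. The check is one of sign.

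**Inputs from the article**

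1. Definition: arousal corresponds to an increase in heart rate variability (Psychophysiological arousal).
2. Intended effect: the intervention lowers arousal (Intervention).
3. Reference segment: the 5-minute baseline, followed by the interview and imagery segments of 5 minutes each (Psychophysiological arousal).

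**Input from outside the article, taken as an assumption**

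4. Heart rate variability tends to fall with stress and to rise with slow breathing. This is general physiological knowledge. The article does not state it, and the references attached to the sentence could not be consulted. The assumption applies to an index for which a larger value means more beat-to-beat variability.

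**Sign check.** For a participant at one visit, let

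D = variability during the interview or imagery segment − variability during the baseline segment.

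- Under input 4, a challenge that arouses the participant makes D negative. A calmer participant has a D that is less negative, or even positive.
- If breathing retraining works as input 2 intends, D should therefore be higher on average in the BREATHE arm than under treatment as usual (TAU): D(BREATHE) − D(TAU) > 0.
- By the stated definition, arousal moves with +D. The positive difference is read as more arousal in the BREATHE arm.
- By the accepted direction, arousal moves with −D. The same positive difference is read as less arousal in the BREATHE arm.

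The same holds across visits. If variability is higher after treatment than at the baseline visit, the stated definition reads this as arousal having risen, and the accepted direction reads it as arousal having fallen.

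**Search for a correction elsewhere.** The Treatment mechanisms sections, the assessment schedule in Table 1 and Quantitative data analyses contain no statement that reverses or qualifies the direction.

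**The case against.** The strongest reply is that this is loose drafting of a minor measure. The sentence compresses two instruments into one clause: read literally, a skin-response system is used to measure heart rate variability. The word for increase may have been meant for skin response, or for the hoped-for change after treatment. The direction also rests on knowledge from outside the document. These points are fair, and they lower the weight of the finding. They do not remove it, because the text as published equates arousal with rising variability, and either charitable reading needs the same one-sentence correction.

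It is also fair that the measure is conditional and exploratory, and that arousal has a second, self-reported measure, the Self-Assessment Manikin, scheduled at every assessment. The mechanism does not depend on this measure alone.

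Four stronger readings are tempting, and the article does not support them.

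- **A benefit would be reported as a worsening of the same size.** The article gives no scoring algorithm. Variability summarised by arm and segment keeps its own sign. The error enters only when those values are interpreted as arousal by the stated definition.
- **The two sensors would contradict each other.** Skin response has no stated direction, so a conflict is an inference.
- **A measurement period is missing.** The phrase "before during and after discussion of the trauma experiences and symptoms" describes the published challenge interview rather than this trial's recording plan. Imagery, listed last, can serve as the segment after the discussion. The three segments add up to the stated total (5 + 5 + 5 = 15 minutes), and no recovery period is promised.
- **Heart rate itself should be added as an outcome.** The section does not name it as one, and correcting the direction does not require it.

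**Conclusion.** The point holds as a misdirected definition. Applied literally, it would turn a calming effect into apparent arousal on this measure.

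Its size is limited. It affects the interpretation of one exploratory mechanism measure, used only if usability testing is favourable. It does not touch recruitment, retention, satisfaction, fidelity or the planned sample size, and no numerical bias can be stated because no index or scoring rule is given.

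The conclusion rests on two assumptions: that the usual physiological direction applies to the index eventually used, and that the sentence is applied as written. If the authors intended something else, the analysis may come out right, but the published definition would still be wrong. A reader might infer that the later trial would drop or mis-specify the mechanism. The article does not support that: its Discussion ties a future trial to acceptability and to whether implementation problems can be solved.

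**What to change.** Replace the defining sentence with one that gives each channel its own direction. For example: greater physiological arousal is indicated by a decrease in heart rate variability from the 5-minute baseline segment to the trauma interview and trauma imagery segments; separately, an increase in skin conductance over the same segments indicates greater arousal. Naming the variability index in the same sentence, or in the analysis plan, would settle the direction fully. No new outcome and no change to the recording schedule is needed.

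The cost is one sentence. Trial status says recruitment had not begun, so at that version the change could be made before any data were collected. If collection has since started, it can still be made before the recordings are scored, with no effect on participants or procedures.

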### Use of stress management strategies

For participants in the intervention condition, use of stress management strategies that are taught during the intervention, including breathing retraining and positive coping skills, will be assessed by therapists during in-session homework review, and will be validated by fidelity raters when they review the audio-recorded sessions.

### Mental health symptoms and functional impairment

#### Suicidal ideation

Suicidal ideation will be assessed using the Suicidal Ideation module of the CIDI [74].

#### Alcohol misuse

Hazardous alcohol use will be assessed using the Fast Alcohol Screening Test (FAST) [93] adapted to include conversions for local alcoholic beverages [94].

### Clinician-rated PTSD symptoms and diagnosis

Psychiatric nurses will interview participants using the past-month version of the Clinician Administered PTSD Scale for DSM-5 (CAPS-5). Nurses will score participants to generate an overall symptom severity and cluster ratings. They will also use the score on the CAPS-5 to decide about whether or not participants meet current DSM-5 diagnostic criteria for PTSD.

### Self-reported PTSD symptoms

PTSD symptoms in reference to the initially identified traumatic event will be assessed using the Ethiopia adapted version of the PTSD Checklist for DSM-5 (PCL-5) [95].

### Functional impairment

Functional impairment will be assessed by the WHO Disability Assessment Schedule II (WHODAS 2.0) 12 item version, which has been used previously in Ethiopia [96, 97].

### Depression symptoms

Depression symptoms will be measured by an adapted version of the Patient Health Questionnaire (PHQ-9) [98] which has been adapted for and used in Ethiopia [99].

#### Intervention satisfaction

Participants and caregivers will complete satisfaction ratings that have been developed and validated in Ethiopia [47] during their post-assessment and providers will complete ratings of their perception of participant satisfaction, after the participant’s last treatment session.

### Feasibility trial assessment schedule

Quantitative assessments will be conducted by masked data collectors and psychiatric nurses at baseline, post-treatment: defined as the same day up to 1 week after the last session (post), 1-month after treatment completion (1-month follow-up), and 3-months after treatment completion (3-month follow-up; see Fig. 1 and Table 1). Intervention and healthcare satisfaction ratings will be completed by providers and caregivers (with participant consent) at post-assessment. Qualitative interviews with participants who will be purposively sampled based on those who do and do not complete all of the treatment sessions and those who do and do not have positive symptom improvement will be conducted during the 1-month follow-up by a different researcher to preserve blinding. Participants who do not want to continue therapy sessions may still participate in assessments.

**Table 1 Tab1:** SPIRIT 2013 figure

	Screening	Enrolment	Allocation	Study period				
				Post-allocation				Close-out
**Timepoint**				**Sessions 1–5**	**+< 1 week**	**+ 1 month**	**+ 3 month**	
**Enrolment**								
**Eligibility screen**	X							
**Informed consent for Full Assessment**	X							
***Full Assessment screen***	X							
**Informed Consent for Trial**		X						
**Allocation**			X					
**Interventions**								
***BREATHE Ethiopia***				X				
***Treatment as usual***				X				
**Assessments**								
*Sociodemographics questionnaire*	X				X	X	X	
*Life Events Checklist for DSM-5*	X				X	X	X	
*adapted PTSD Checklist for DSM-5* (PCL-5)	X				X	X	X	
*WHO Disability Assessment Schedule II WHODAS-2 (12-item)*	X				X	X	X	
*Clinician Administered PTSD Scale for DSM-5 (CAPS-5)*		X			X	X	X	
*Brief Psychiatric Rating Scale Expanded Version 4.0 (BPRS-4.0)*		X			X	X	X	
*Suicidal Ideation module of the CIDI*		X			X	X	X	
*adapted PTSD Knowledge Test*		X			X	X	X	
*Internalized Stigma of Mental Illness Scale (ISMI-10)*		X			X	X	X	
*Post-Traumatic Cognitions Inventory*		X			X	X	X	
*The Self-Assessment Manikin (SAM)*		X			X	X	X	
*PhenX Toolkit’s trauma challenge assessment*		X			X	X	X	
*Use of Stress Management Strategies*		X		X	X	X	X	
*Fast Alcohol Screening Test (FAST)*		X			X	X	X	
*Patient Health Questionnaire (PHQ-9)*		X			X	X	X	
*Intervention and healthcare satisfaction ratings*					X			
*Qualitative interview*					X	X		

The time from initial contact to each assessment and each treatment session will be tracked. To allow for scheduling flexibility, participants will be able to complete each assessment up to 1 week before or after the target assessment date, for a total of a 2-week assessment window for the 1-month and 3-month follow-ups, and a 1-week assessment window for the post-assessment.

Since intervention participants may take between 5 weeks to 5 months to complete the intervention, participants in the TAU condition will be matched by study enrollment date and health center location to a participant in the intervention condition, and will complete follow-up dates on the same schedule. Since interview times may differ by participant, participants will be told they will complete five sessions and four interviews during the study, but will not be told the assessment schedule in advance.

Assessments will take place at the primary care center or hospital, unless this is not feasible for participants. If participants cannot come to the primary care center for assessments, then the assessments will be completed in participant’s homes or another location of their choice. All intervention and TAU sessions will take place in the health care center, and all participants will continue concomitant medication management and follow-up care.

When participants are initially consented for the trial, participants will be given a phone number and a 25 Ethiopian Birr (ETB) phone card to use to contact researchers about scheduling or questions or if they experience any adverse events. In addition, they will be asked how they would like to be contacted in the event that they have missed a session. Options will include a phone call or home visit by a researcher or no contact. If participants select a phone call or home visit, providers will attempt to contact them three times before discontinuing them from the study.

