### Intervention

BREATHE Ethiopia is a treatment for post-traumatic stress disorder (PTSD) symptoms for use with individuals who have a diagnosis of PTSD or “probable PTSD.” This program is adapted from the “B.R.E.A.T.H.E.—Brief Relaxation, Education and Trauma HEaling: A Brief Intervention for Persons with PTSD and Co-Occurring Serious Mental Health Conditions” [79].

This intervention is designed to be delivered in primary care and fits within the Ethiopian Ministry of Health’s mandate to expand the care for people living with mental health conditions. Given the technical challenges in the field the intervention is designed to be delivered in person and has been adapted to follow mitigation procedures as per current ongoing restrictions. The program meets the guidelines provided by the World Health Organization’s Mental Health Gap Action Program (mhGAP) module on the Assessment and Management of Conditions Specifically Related to Stress [1]. The intervention was culturally and contextually adapted using qualitative semi-structured interview data from 48 participants including patients with SMI (*n* = 13); caregivers of patients with SMI (*n* = 13); health care providers (*n* = 13); and community and religious leaders (*n* = 9) from Sodo District, Ethiopia [80]. Adaptations were made to the intervention delivery and content.

Intervention delivery adaptations included changing (1) the session number and length from three 50-min sessions to five 20- to 30-min sessions, to accommodate the needs of the primary health care centers; and (2) the frequency of sessions from once a week to anywhere from once a week to once a month, to accommodate travel difficulties for patients and to map onto the normal frequency with which patients visit the primary care facilities for medication management follow-up visits. Content adaptations included (1) adding in positive coping skills and practices that were identified from the qualitative data and that were feasible in the rural Ethiopian context, such as purposeful engagement in positive activities; (2) changing the language to be more acceptable and understandable in Amharic (for example, changing “hyperarousal” to “over alertness”); (3) adding in psychoeducation about SMI symptoms and stigma; and (4) providing more guidance to providers on communication strategies, specifically ways to present the intervention in encouraging, normalizing, and non-stigmatizing ways.

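### A missed session can end study participation, and early stoppers and their TAU matches have no workable assessment dates, so assessment retention partly reflects attendance

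*Protocol article*

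**What the plan says.** All references are to the protocol article.

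- **Missed sessions** (Feasibility trial assessment schedule, text after Table 1). At consent, participants say how they wish to be contacted if they miss a session: "Options will include a phone call or home visit by a researcher or no contact". For those who choose a call or visit, "providers will attempt to contact them three times before discontinuing them from the study". No arm is named, and no consequence is given for those who choose no contact.
- **Stopping therapy** (same section, opening paragraph). "Participants who do not want to continue therapy sessions may still participate in assessments".
- **Assessment dates** (same paragraph). Post-treatment is "defined as the same day up to 1 week after the last session (post"), and the later visits are "1-month after treatment completion (1-month follow-up), and 3-months after treatment completion".
- **Session spacing** (Intervention). The adaptation changed "the frequency of sessions from once a week to anywhere from once a week to once a month".
- **TAU dates** (Feasibility trial assessment schedule). "participants in the TAU condition will be matched by study enrollment date and health center location to a participant in the intervention condition", and they follow that person's assessment schedule.
- **Interviews** (same section, and Qualitative interviews). The 1-month interviews are to include people who did not complete all sessions and people who dropped out of treatment.
- **Retention** (Participation and retention). Sessions completed are counted in the intervention arm. Assessments completed are counted in all trial participants.

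**The concern.** Leaving treatment and leaving the study are different events, and the article does not keep them apart. A person who announces that they are stopping sessions keeps follow-up. A person who simply stops coming and is not reached in three attempts loses it. The second kind of stopping is probably the one more closely tied to poor engagement, so the outcomes lost would not be a random subset.

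The dating rule adds to this. It presupposes that the end of treatment is known when it happens, which is not so for someone who stops silently.

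The stake is mainly the feasibility result. The abstract lists the number who engage in treatment and the number who complete assessments as separate facts needed for the future trial. If the second depends partly on the first through a discontinuation rule, the future trial's dropout allowance rests on a figure that the rule itself helped to produce. The exploratory comparison of outcomes between arms is affected too. A mixed model or multiple imputation cannot fully repair outcomes that were never collected if their absence depends on the unobserved outcome.

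**Working it through.** **1. The passages side by side.**

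| Situation | Session rule | Assessment rule |
|---|---|---|
| Declines further therapy, in contact | Stops sessions | May still be assessed |
| Misses a session, chose call or visit, not reached in three attempts | Discontinued from the study | None remains |
| Misses a session, chose no contact | Not stated | Not stated |

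The second row cannot be squared with the plan to sample treatment dropouts at the 1-month visit, except for dropouts who stayed in touch.

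**2. When an early stop becomes visible.** Take day 0 as the last session attended and about 30 days as a month.

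- Post window: day 0 to day 7.
- Weekly spacing: first missed session at about day 7. 7 − 7 = 0 days remain, before any contact attempt.
- Monthly spacing: first missed session at about day 30. 30 − 7 = 23 days after the window closed.
- 1-month visit, if counted from the last session attended: window of one week either side, so day 23 to day 37. On monthly spacing, 37 − 30 = 7 days remain for contact and assessment.

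If treatment completion means the fifth session, it never occurs for an early stopper and the 1- and 3-month visits have no date at all. Because TAU dates are copied from the matched BREATHE participant, the TAU match is left undated as well.

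**3. The only dropout figure in the article.** Randomization states 45 randomised to allow for dropout; the trial design section gives n = 40. The implied allowance is (45 − 40)/45 = 11.1%. No dropout rate is stated, so this is a consistency check and not a reproduction. If all five losses fell in one arm, that would be 5/23 = 21.7% to 5/22 = 22.7% of it.

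**4. Illustrative size.** The article gives no non-completion rate, no unreachable share and no outcome difference. All three are assumed here:

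- *c*, share of BREATHE participants who do not complete: 10% to 40%
- *u*, share of those who are not reached: 0, one half or all
- *g*, extra improvement of completers over non-completers: 0.5 SD
- arm size 45/2 = 22.5

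Number lost = 22.5 × *c* × *u*. Shift in the observed BREATHE mean = *g* × [*c* − *c*(1 − *u*)/(1 − *cu*)].

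| *c* | *u* | Lost | Shift (SD) |
|---|---|---|---|
| 10–40% | 0 | 0 | 0 |
| 10% | ½ | 1.1 | 0.024 |
| 20% | ½ | 2.2 | 0.044 |
| 40% | ½ | 4.5 | 0.075 |
| 20% | 1 | 4.5 | 0.10 |
| 40% | 1 | 9.0 | 0.20 |

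The shift is proportional to *g*: the last row becomes 0.10 SD at *g* = 0.25 and 0.40 SD at *g* = 1.0. It is the shift in a simple observed mean. The planned mixed model may reduce it.

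**The case against.** A reader might infer that the plan loses the outcomes of all non-completers, and only in the BREATHE arm. The documents do not support either part.

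- People who decline further therapy may still be assessed, home assessment is allowed, and dropouts are to be interviewed at the 1-month visit. Only non-completers who are not reached are at risk, and some of those could not be assessed under any rule.
- The missed-session rule names no arm. The article refers to TAU sessions and tells all participants to expect five sessions. Greater loss in BREATHE is plausible, since only there is session completion counted and TAU is medication management and follow-up. That remains an inference, and zero loss in TAU cannot be claimed.
- The group choosing no contact is not said to be discontinued. The sentence covers only those who choose a call or visit.
- The retention section defines attendance and assessment completion separately, so they are not confused by definition.
- The trial is descriptive and exploratory, and a condensed article may leave visit dating for early stoppers to the full protocol.

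All of this stands, and it limits the size and the arm claim. It does not remove the conflict. The article itself fixes a rule that ends study participation after unanswered contact about a session, and itself fixes date anchors that fail for early stoppers. Exploratory status is little defence when retention is one of the things the trial is meant to measure.

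**Conclusion.** The concern holds in limited form. Two faults follow from the text alone: discontinuation from the study conflicts with continued assessment and with the planned sampling of dropouts, and the assessment dates do not work for silent early stoppers or for their TAU matches. The delay of about 23 days applies to monthly sessions with unannounced stopping.

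The consequence is a possible loss of obtainable outcomes among unreached non-completers, probably more often in BREATHE, and an assessment-retention figure that partly reflects attendance. The size is not known. The range of 0 to 9 BREATHE participants and 0 to 0.2 SD rests on the assumed 10–40% non-completion, the full range of unreachable shares and a 0.5 SD difference. The upper end needs every non-completer to be unreachable. The faults should be corrected before enrolment, because assessments not made cannot be recovered afterwards.

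**What to change.** Reconcile the passages as follows, for outcome follow-up only:

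1. State that missing or stopping sessions does not by itself end participation in the study. Post, 1-month and 3-month assessments are still offered, at home if needed, unless the participant withdraws consent for assessments.
2. Ask contact preference for assessments separately from preference for missed sessions, and say what choosing no contact about sessions means for assessments.
3. For early stoppers and their TAU matches, set the post date from randomisation, for example at the planned end of the five-session course, and date the 1- and 3-month visits from it. Because the course may take 5 weeks to 5 months, state how the planned end is fixed for each participant.

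Rules on continuing or stopping sessions are left to the investigators. The cost is protocol wording plus some extra contact attempts and home assessments. Home assessment is already permitted, and the Trial status section says recruitment had not started.
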